## 3. Methods

This will be a multicentric randomized controlled trial with blinded outcome assessments coordinated by the Department of Mental and Physical Health and Preventive Medicine at the University of Campania Luigi Vanvitelli, and it will be conducted in 24 Italian outpatient clinics.

Eligible patients and their families will be identified by their treating clinicians and referred to the specialized staff to be included in the study. After acceptance, an informed consent form will be signed and an appointment for baseline assessments will be made. Consent can be withdrawn at any time by both patients and their relatives. Patients will be randomly assigned in a 1:1 ratio to the experimental group or the control group. The randomization will be stratified according to the recruiting center and each patient’s age, sex, and educational level. The procedure will be implemented in the coordinating center using specific statistical software. The researchers and statisticians involved in the patients’ assessments will be blinded each patient’s allocation. The mental health professionals providing the interventions will not be blinded to the patients’ allocations.

Patients referred to the outpatient units of participating mental health centers will be invited to participate in the study if they meet the following inclusion criteria: (1) diagnosed with MDD according to the Diagnostic and Statistical Manual of Mental Disorders, Fifth Edition (DSM-5); (2) between 18 and 65 years of age; (3) admitted to the local mental health center for at least 6 months, with at least one access per month; (4) ability to provide written informed consent; (5) cohabitation with at least one family member.

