### 8.3. Exploratory Outcomes

The presence of childhood traumas and certain affective temperaments (i.e., cyclothymic, irritable, and hyperthymic temperaments) can be considered possible predictors and/or mediators of response to psychosocial treatments. Thus, these risk factors will be included as possible moderators in order to assess the influence of these variables on the efficacy of the experimental intervention. Additionally, a series of clinical indicators of illness severity will be collected (including age at onset of the first episode, previous psychiatric hospitalizations, number and type of suicide attempts, alcohol and drug use, presence of psychotic symptoms during acute phases, severity of symptoms at baseline, and adherence to pharmacological treatments), and these will be used as explanative variables. Multivariable models will be corrected for these variables in order to identify patients who are more likely to be responsive to the effects of PFIs.

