## 9. Statistical Analyses

### 9.1. Power Analysis

The sample size was estimated with respect to the measurement of the main outcomes of the study, and the measure that required the largest sample size (HAM-D) was taken as the reference. Specifically, a sample size sufficient to reduce the total HAM-D score by 10%, with a two-tailed probability of 0.05% and a power of 90%, was estimated. The multicenter design of the study required an adjustment of the sample size estimate in accordance with the value of the intracluster correlation coefficient, set at 0.030, and the coefficient of variation of cluster sizes, set at 0.400. The estimated sample size is 176 patients, 88 for each arm. Based on previous studies conducted with similar patient populations, a dropout rate of 15% is expected. Therefore, it will be necessary to recruit 384 families, 192 for each arm. Each participating center is expected to recruit 16 families (8 for each arm).

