### 9.2. Statistical Analyses

The statistical analyses will be conducted in accordance with the intention-to-treat analysis. Missing data will be handled using a last observation carried forward (LOCF) analysis. Descriptive statistics will be calculated for the dependent and confounding variables for both groups. Confidence intervals will be calculated at 95%.

The analytical plan will include the following: (1) the use of generalized estimating equations (GEEs), which will provide an estimation of the impact of the intervention on the primary and secondary outcomes while controlling for multiple confounders (i.e., age, gender, illness duration, number of previous relapses, severity of symptoms at baseline, previous psychiatric admissions, physical and mental comorbidities, presence of psychotic symptoms during acute phases, suicidality, pharmacological treatments); (2) the application of a structural equation model to identify possible mediators and moderators of intervention efficacy (i.e., specific temperamental profiles, the presence of childhood trauma and/or abuse, severity of symptoms at baseline, the patient’s psychosocial functioning at baseline, number of family members, the relatives’ coping strategies and levels of expressed emotions at baseline); and (3) the use of a multivariate logistic regression model to identify predictors of a poor response to the experimental intervention.

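### The GEE covariate list omits centre and educational level, two of the four stratification factors, and does not tie suicidality or drug treatment to baseline

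*Protocol article*

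**What the plan says.** **Design.** Section 3 (Methods) states: "The randomization will be stratified according to the recruiting center and each patient’s age, sex, and educational level". The Abstract gives the same four factors. Allocation is 1:1, and Section 9.1 expects 16 families per centre, 8 in each arm, so families are randomised within centres.

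**Analysis.** Section 9.2 plans GEEs for the primary and secondary outcomes "while controlling for multiple confounders (i.e., age, gender, illness duration, number of previous relapses, severity of symptoms at baseline", and the list continues with "previous psychiatric admissions, physical and mental comorbidities, presence of psychotic symptoms during acute phases, suicidality, pharmacological treatments". That makes ten items. Age and gender are there; centre and educational level are not. The section does not state the GEE clustering unit.

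**Sample size.** Section 9.1 says the multicentre design called for an adjustment by the intracluster correlation coefficient, "set at 0.030, and the coefficient of variation of cluster sizes, set at 0.400".

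**Timing.** Table 2 has the patients' schedule (which records pharmacological interventions), the C-SSRS (suicidality) and the adherence scale all collected at T0, T1, T2 and T3.

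**Adherence.** It is not in the GEE list. Section 8.3 (Exploratory Outcomes) names it without a time point among clinical indicators: "severity of symptoms at baseline, and adherence to pharmacological treatments), and these will be used as explanative variables". Sections 2 and 8.2 also make better adherence a secondary outcome.

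**The concern.** A trial that stratifies its randomisation should normally carry the stratification factors into the analysis. Balance on a prognostic factor reduces the true variance of the treatment comparison, but a model without that factor leaves its variance in the error term. The reported standard error is then larger than the real one, intervals are too wide, and some power is lost. Here two of the four factors are carried forward and two are not, with no reason given. Centre is also treated unevenly: it enters the sample size but not the stated model.

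The second issue is the time point. Section 9.2 writes *at baseline* for symptom severity, and again for several items in its list of possible mediators and moderators, but not for suicidality or pharmacological treatments. The article gives reason to think the intervention could change both: Section 4 describes sessions on drug treatment and on the effects of stopping it abruptly, plus a suicide-risk session for some patients, and Section 10 cites studies suggesting a role in preventing suicidality. If follow-up values entered the model, part of the effect under test could be removed.

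**Working it through.** **1. The plan's own figure.** The 176 patients in Section 9.1 cannot be rebuilt, because no SD or baseline mean for the HAM-D is given. The recruitment target does not follow from it either: 176 / 0.85 = 207.1, or 208 as an even number, while 384 = 24 × 16. That is a separate matter and does not bear on the covariate list.

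**2. Standard error when balanced strata are left out.** If the omitted factors explain a share v of the outcome variance and are balanced between arms, the model-based SE is too large by the factor 1/√(1 − v). The corresponding two-sided type I error is 2 × [1 − Φ(1.96/√(1 − v))]. Treating the plan's ICC as the share due to centre gives:

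| Omitted | v | SE factor | Type I error (nominal 5%) |
|---|---|---|---|
| Centre, ICC 0.03 (plan) | 0.03 | 1/√0.97 = 1.015 | 4.7% |
| Centre + education 2% (assumption) | 0.05 | 1/√0.95 = 1.026 | 4.4% |
| Centre + education 5% (assumption) | 0.08 | 1/√0.92 = 1.043 | 4.1% |

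In terms of information, the first row is like analysing 384 × 0.97 ≈ 372 families, and the last like 384 × 0.92 ≈ 353.

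**3. Simulation check.** 24 centres of 16 (8 per arm), education balanced within centre and arm, no treatment effect, 8,000 runs per setting:

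| ICC | Education share | Mean SE without / with both factors | Rejection without / with |
|---|---|---|---|
| 0.03 | 0 | 0.1019 / 0.1004 | 5.2% / 5.5% |
| 0.03 | 0.02 | 0.1019 / 0.0994 | 4.3% / 4.7% |
| 0.03 | 0.05 | 0.1019 / 0.0978 | 4.2% / 5.1% |
| 0.10 (assumption) | 0.05 | 0.1018 / 0.0941 | 3.3% / 5.1% |

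The SE ratios agree with the formula (0.1019/0.0978 = 1.042). The Monte Carlo error of a 5% rejection rate is √(0.05 × 0.95/8000) ≈ 0.24 percentage points, so in the first row the loss shows in the SE but is too small to read from the rejection rates.

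**4. Post-randomisation covariates.** If treatment moves a follow-up covariate by a, and that covariate moves the outcome by b (both standardised), adjusting for it removes a × b of the effect d. With d = 0.35 and a and b each between 0.1 and 0.3 (all assumptions), the share removed runs from 0.01/0.35 = 3% to 0.09/0.35 = 26%. With T0 values it is zero.

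**5. The adjustment in Section 9.1.** The article prints neither the formula nor the cluster size. If the usual whole-centre formula was used, the design effect is 1 + [(1 + CV²)m − 1] × ICC, with CV² = 0.16:
- m = 176/24 = 7.33: 1 + (8.507 − 1) × 0.03 = 1.225
- m = 16: 1 + (18.56 − 1) × 0.03 = 1.527

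With randomisation within centres and centre in the model, the factor is about 1 − 0.03 = 0.97. The overstatement would then be 1.225/0.97 = 1.26 (26%) or 1.527/0.97 = 1.57 (57%), depending on m.

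**The case against.** **Centre may already be handled.** In a GEE, centre can be the cluster identifier and would then not appear among the covariates. Section 9.1 shows that the authors had centre clustering in mind. This stands: in that case the standard-error effect is reduced or absent. But the article does not say so, and the printed list is closed.

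**The size is trivial and the direction safe.** Largely true. At the plan's own ICC the SE is 1.5% too large and no false positives are created. With two levels each of age, sex and education (assumption) there are 24 × 2 × 2 × 2 = 192 strata for 384 patients, about two per stratum. Balance may therefore be incomplete and the effect smaller than computed.

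**Covariates called confounders are naturally baseline values.** Section 7 says that clinical characteristics are collected at baseline, and several listed items are history by nature. An article may also leave time points to a fuller document. This is fair, and it is why the point goes no further than saying that follow-up values are not excluded. Still, the section marks baseline for some items and not for these two.

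**Stronger readings that the text does not support.** A reader might infer that the GEE adjusts for adherence and so removes part of the effect. Adherence is not in that list; it belongs to the exploratory models for identifying likely responders. A reader might also infer that the sample size is overstated by 57%. That needs both the whole-centre formula and 16 per centre, and neither is stated. Delivery by two trained professionals per centre (Section 5) is another possible source of clustering.

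**Conclusion.** The point holds in a limited form. Centre and educational level are stratification factors missing from a closed GEE covariate list, and this conflicts with Sections 3 and 9.1. Unless the GEE clusters on centre, the standard errors are about 1.5% too large for centre alone at ICC 0.03, and about 2.6% to 4.3% too large if education explains a further 2% to 5% of variance. The first figure rests on the plan's ICC and on balance within centres; the second also on an assumed share for education. The consequence is some lost precision, not a false positive result, so it would be wrong to conclude that the primary test is invalid.

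For suicidality and pharmacological treatments, adjustment for post-randomisation values is a possibility left open, not a stated plan. The 3% to 26% range shows what would be at stake under assumed paths and is not a forecast. Adherence raises the same timing question, but only in the exploratory models. Any overstatement of the sample size from the ICC and CV adjustment cannot be fixed from the article.

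**What to change.** - **Section 9.2, primary model:** add centre (fixed effect, or random intercept in a mixed model) and educational level beside age, sex and baseline score. If the intention is a GEE clustered on centre, say so.
- **Sections 9.2 and 8.3, timing:** specify that suicidality, drug treatment and adherence, wherever used as covariates, are T0 values.
- **Section 9.1:** state the formula and cluster size behind the ICC and CV adjustment, and reconcile it with randomisation within centres, or name the other source of clustering that it is meant to cover.

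The cost is wording. The model change uses 23 degrees of freedom for centre (24 − 1) plus one fewer than the number of education levels, which is negligible with 384 families. No new data are needed: centre is known from recruitment, and Table 2 already collects education, suicidality, drug treatment and adherence at T0.

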## Abstract

This study aims to assess the efficacy of a psychoeducational family intervention (PFI) to reduce the severity of depressive symptoms and to improve psychosocial functioning and to increase social contacts in a sample of patients with major depressive disorder (MDD). The degree to which PFI will reduce patients’ relapses, hospitalizations, and self-stigmatization and will improve their quality of life will also be assessed. Other secondary outcomes include the improvement of relatives’ coping strategies, family burden, expressed emotions and quality of life. This non-profit, unfunded, national, multicentric randomized controlled trial with blinded outcome assessments will be carried out in 24 Italian university outpatient units. Families will be assessed at baseline and at 6, 12, and 24 months post-randomization. Our working hypothesis is that the PFIs will reduce the patients’ severity of depressive symptoms, their relapses, and their hospitalizations, and that they will improve their psychosocial functioning and quality of life. We expect these results to be maintained after 12 and 24 months, albeit with a reduction in magnitude. The sample will consist of 384 patients randomized at a 1:1 ratio and stratified according to center, age, gender, and educational level.

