## 4. Interventions

The experimental intervention will consist of the Falloon psychoeducational family intervention, which was developed for the treatment of schizophrenia [52], but which we have adapted for the treatment of major depression. The experimental intervention will be administered individually to each recruited family and consist of the following six phases: (1) engagement of the family unit; (2) individual assessment; (3) family assessment; (4) informative sessions; (5) communication skills sessions; and (6) problem-solving skills sessions.

The informative sessions will deal with the following issues: (1) clinical characteristics of MDD, symptoms, prognosis, risk and protective factors; (2) available pharmacological and non-pharmacological treatments for MDD, indications, side effects and strategies to cope with them, treatment duration, risk factors for relapse, and effects related to abrupt cessation of the therapy; and (3) early warning signs. A specific informative session on suicide risk has been developed, and this will be administered only to patients who report suicidal ideation during the intervention or who have a history of suicide attempts or ideation.

The sessions will take place three times a month for a period ranging from 4 to 6 months (about 18 sessions in total). The number of sessions, as well as their frequency, may vary depending on each patient’s clinical situation. Sessions will have an average duration of 60–90 min and will require the active participation of all family members, including the patient. Between sessions, participants will be invited to organize “family meetings” to discuss the topics covered during the previous meeting, progress made, and problems encountered in implementing changes. Each meeting will ideally be divided into three phases: a first phase dedicated to clarifications and questions regarding the topics previously discussed, a second phase focused on the main topic of the meeting (the so-called “teaching phase”), and a final phase in which the key points addressed during the session are summarized and in which “homework” is assigned.

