### 8.2. Secondary Outcomes

We expect that, compared with those in the control group, the patients receiving the PFI will report a significantly lower number of relapses and hospitalizations after 12 and 24 months as well as improvements in their adherence to pharmacological treatments, quality of life (evaluated using the Manchester Short Assessment of Quality of Life), and coping strategies, and a reduction in their internalized stigma. With respect to coping strategies, we expect an increase in the relatives’ problem-oriented coping strategies (i.e., maintenance of social interests, involving the patient in social activities, positive communication with the patient, seeking information, talking with friends and/or relatives about the patient’s situation) and a reduction in emotion-focused coping strategies (i.e., collusion, avoidance, resignation, coercion, use of alcohol and/or drugs). Moreover, we expect reductions in objective and subjective family burden and improvements in expressed emotions and quality of life, both at the end of the intervention and at follow-ups.

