**Obtaining approval of ethical committees**													
**Training in the use of assessment instrument**													
**Training in the use of interventions**													
**Recruitment of patients and their relatives**													
**Administration of interventions**													
**Follow-up assessments**													

**Table 2 brainsci-13-01199-t002:** Assessments instruments.

Assessment Tool	Assessed Domains	Description	Study Population	Assessment Time-Points
**Patients’ socio-demographic schedule**	**Patients’ socio-demographic and clinical characteristics**	**Recorded information will include illness duration, age at onset, number of affective episodes and previous hospitalizations, age at first hospitalization, number of suicide attempts, age, gender, educational level, occupational status, and pharmacological and psychosocial interventions.** **The information will be compiled by the researcher in collaboration with the patient. If the information is inadequate, or if the researcher is not sure about the patient’s reliability, other sources (e.g., treating physician, relatives) can be consulted.**	**Patients**	**T0, T1, T2, and T3**
**Relatives’ socio-demographic schedule**	**Relatives’ sociodemographic characteristics**	**Recorded information will include age, gender, educational level, occupational status, nature of relationship with the patient, number of years cohabiting with the patient, and mean number of daily hours spent with the patient.**	**Relatives**	**T0**
Hamilton Depression Rating Scale (HAM-D) [53]	Severity of depressive symptoms	The HAM-D includes 17 items. Of these, eight items are scored from 0 (absent) to 4 (severe), while nine are scored from 0 to 2. The total score is the sum of the item scores, and ranges from 0 to 52 points.	Patients	T0, T1, T2, and T3
Personal and Social Performance Scale (PSP) [54]	Psychosocial functioning	The total score (which can range from 0 to 100) can be used to assess the patient’s overall functioning (higher scores indicate higher functioning). Ratings are based mainly on assessments of a patient’s functioning in four main areas: (1) socially useful activities; (2) personal and social relationships; (3) self-care; and (4) disturbing and aggressive behaviors.	Patients	T0, T1, T2, and T3

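### Relatives' secondary outcomes share one GEE covariate list built around the patient, so the relative's own baseline variables go unused and some precision is lost

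*Protocol article*

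**What the plan says.** All statements are in the protocol article.

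- **Model.** Section 9.2 plans GEEs that "will provide an estimation of the impact of the intervention on the primary and secondary outcomes while controlling for multiple confounders". No separate model for relatives is given.
- **Covariates.** The list is introduced by i.e., so it reads as closed. The wording is "controlling for multiple confounders (i.e., age, gender, illness duration, number of previous relapses, severity of symptoms at baseline, previous psychiatric admissions", and it goes on to comorbidities, psychotic symptoms in acute phases, suicidality and drug treatment.
- **Outcomes covered.** The Abstract states: "Other secondary outcomes include the improvement of relatives’ coping strategies, family burden, expressed emotions and quality of life". Section 8.2 repeats this: "we expect reductions in objective and subjective family burden and improvements in expressed emotions and quality of life". Table 2 has relatives complete the FPQ, LEE, MANSA and FCQ at T0 and at every follow-up.
- **Relatives' own data.** The relatives' schedule in Table 2, taken at T0, records age, gender, education and occupation, and also "nature of relationship with the patient, number of years cohabiting with the patient, and mean number of daily hours spent with the patient".
- **Other use of relatives' data.** The structural equation model in section 9.2 takes relatives' baseline coping and expressed emotion, and the number of family members, as possible mediators or moderators.
- **Relatives per family.** Eligibility in section 3 requires "cohabitation with at least one family member". Intervention sessions in section 4 "will require the active participation of all family members, including the patient". Section 7 gives an assessment time for each relative. Nowhere is the number of relatives assessed per family given.
- **Clustering.** The only clustering mentioned is by centre, in the power analysis of section 9.1. The GEE cluster unit is not stated for any outcome.

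**The concern.** The covariate list suits a patient outcome such as the HAM-D. Applied as written to a caregiver's burden or coping score, it would adjust for the patient's psychotic symptoms and admissions but not for who the caregiver is, how much time they spend with the patient, or how they scored on the same scale at T0. The baseline value of an outcome is usually its strongest predictor. Because the article gives an explicit closed list for these outcomes, this is a stated choice that fits them poorly, and not merely a detail left for later.

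At stake is the width of the confidence intervals for the relatives' outcomes, which are a stated aim of a family intervention (section 2, items 4 and 5). Leaving out prognostic covariates does not bias a randomised comparison.

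A second question follows. A family can include several relatives who share one allocation, so the cluster unit matters for their standard errors, and it is not stated.

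**Working it through.** The article gives no figure for the relatives' outcomes, so there is none to reproduce. It also gives no variance explained, no correlations and no number of relatives per family. Every size below therefore rests on a labelled assumption.

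**1. Which covariates describe whom**

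| Variable | Recorded at T0? | In the GEE list? |
|---|---|---|
| Patient illness and treatment items | yes | yes |
| Age, gender | yes, for both persons | yes, but whose is not said |
| Relative's kinship, years of cohabitation, daily contact hours | yes (Table 2) | no, and in no other named model |
| Relative's own baseline FPQ, LEE, MANSA or FCQ score | yes (Table 2) | no (baseline coping and expressed emotion appear only in the structural equation model) |

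**2. Precision forgone by omitting the relative's characteristics**

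Assume they explain a further share q of residual variance. The standard error is then multiplied by √(1 − q).

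- q = 0.05: √0.95 = 0.975, a fall of 2.5%.
- q = 0.15: √0.85 = 0.922, a fall of 7.8%.

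In terms of sample size, this equals 1/0.95 = 1.05 to 1/0.85 = 1.18 times as many families.

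**3. Precision forgone by omitting the relative's baseline score**

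Assume a baseline-to-follow-up correlation r, given the covariates already listed. The factor is √(1 − r²).

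- r = 0.3: √0.91 = 0.954, a fall of about 5%.
- r = 0.5: √0.75 = 0.866, a fall of about 13%.
- r = 0.7: √0.51 = 0.714, a fall of about 29%.

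If T0 enters the GEE as one of the repeated outcomes, the baseline score is already in use and this gain should not be counted again.

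**4. The cluster unit (conditional)**

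Suppose k relatives per family are assessed, with within-family correlation ρ, and each is analysed as an independent subject. The variance is understated by DE = 1 + (k − 1)ρ, and the true two-sided error at nominal 5% is 2[1 − Φ(1.96/√DE)].

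| k | ρ | DE | SE too small by | True error |
|---|---|---|---|---|
| 1 | any | 1.0 | 0% | 5.0% |
| 2 | 0.2 | 1.2 | 9% | 7.4% |
| 2 | 0.5 | 1.5 | 18% | 11.0% |
| 3 | 0.2 | 1.4 | 15% | 9.8% |
| 3 | 0.5 | 2.0 | 29% | 16.6% |

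A simulation of 3,000 trials under no effect supports the formula. It used 326 families (384 × 0.85), two relatives each and three visits, with variance components of 0.3 for family, 0.3 for relative and 0.4 residual. The correlation between two relatives' means is 0.3/(0.3 + 0.3 + 0.4/3) = 0.41. With robust variance, the rejection rate was 10.5% clustering on the relative (theory 9.9%) and 5.8% clustering on the family (theory 5.0%).

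With the family as cluster, or the centre, which contains whole families, robust variance already allows for correlation between relatives and this inflation does not arise.

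**The case against.** The strongest case against the point is that it asks for an improvement and identifies no error. Omitted covariates do not bias a randomised comparison, the outcomes are secondary, and the gain in precision is assumed. All of that stands and limits the weight of the point. What remains is that a closed list has been stated for outcomes it does not fit, while better-fitting variables are already on the T0 forms.

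Three stronger readings are tempting, and the article does not support them.

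- **That the relatives' standard errors are too small.** This needs two things the text does not say: that several relatives per family are assessed, and that each is treated as independent. The phrases that suggest several relatives concern patient eligibility, session attendance and the duration of an assessment. The cluster unit is commonly left to an analysis plan, so silence about it is no fault. The error rates in step 4 describe an assumed analysis of an assumed sample.
- **That only patient covariates are used and the relatives' data are wasted.** Age and gender may be the relative's, and relatives' baseline coping and expressed emotion enter the structural equation model.
- **That the patient list should be replaced.** The Introduction reports that relatives' anxiety and depressive symptoms recede as the patient's depression improves, and the Discussion links family burden to patients' adherence. Dropping patient severity could lose precision.

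**Conclusion.** The point holds as a low-cost improvement to the analysis of secondary outcomes. Read as written, section 9.2 leaves the relatives' outcomes without adjustment for kinship, cohabitation, contact hours and, unless T0 is modelled as a repeated outcome, the relative's own baseline score. Age and sex may or may not be the relative's.

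The cost is precision alone. It is about 2.5–8% of the standard error if the relative's characteristics explain a further 5–15% of residual variance, and more if the baseline score is also unused. These percentages are assumptions, because the article has no figures from which to derive them.

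Type I error would rise, to about 7–11% with two relatives and a correlation of 0.2–0.5, only if several relatives per family were assessed and treated as independent. With one relative per family, or with family or centre as the cluster, there is no inflation. The primary patient outcomes are not affected.

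**What to change.** Add a short paragraph to section 9.2, or to the analysis plan, for the FPQ, FCQ, LEE and MANSA completed by relatives:

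- **Covariates:** add the relative's own baseline score on the outcome (unless T0 is modelled as a repeated outcome) and the relative's T0 age, sex, kinship, years of cohabitation and daily contact hours. Keep the patient's baseline severity. Say whose age and gender are meant in the existing list.
- **Cluster:** make the family the GEE cluster, with all its assessed relatives and visits in one cluster and robust variance.
- **Number of relatives:** state how many relatives per family are assessed.

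The cost is a few lines of text and a few extra model terms, few against 384 planned families. No new data, visits or participants are needed. If one relative per family is assessed, the family cluster changes nothing. If several are, the intervals will be wider than under an analysis that treats relatives as independent, and correctly so.
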